## Discussion

6

This protocol describes a randomised pilot clinical trial aimed at assessing the feasibility and efficacy of an integrated psychoeducational intervention for adolescents and young adults with emotional and affective disorders recruited at an acute Transition Psychiatry hospital setting. The implementation of structured and standardised interventions in acute psychiatric settings may offer substantial advantages in terms of treatment adherence, illness awareness, mental health literacy and, more broadly, clinical course and prognosis. Rather than acting on primary prevention, which is no longer feasible once hospitalisation has occurred, such interventions could contribute to improve patients’ capacity to recognise early signs of relapse, increase insight and support continuity of care after discharge. Moreover, the possibility of engaging individuals directly during hospital admission allows for timely monitoring of psychopathological trajectories that are often characterised by clinical instability, high relapse risk, recurrent service utilisation and significant psychosocial impairment. In this perspective, psychoeducation represents a highly promising approach, offering knowledge, cognitive strategies, and relational tools essential for promoting awareness, empowerment, and greater adherence to treatment (9, 26–29). International literature has highlighted how psychoeducational interventions, both individual and group-based, can improve mental health literacy, reduce internalised stigma, increase emotional skills, and implement more adaptive coping strategies (5, 6, 8, 9, 30–32). These dimensions represent key clinical targets, since poor illness awareness, maladaptive emotional regulation, and high internalised stigma have been consistently associated with impaired treatment adherence, increased relapse risk, disengagement from services, and poorer functional recovery. Strengthening these domains during the acute phase is therefore not merely an educational objective but a prognostic intervention.

However, there is still a significant lack of studies focusing on adolescents and young adults, particularly in acute settings. This is probably due to the fact that many mental health systems are clearly divided into pediatric services (childhood/adolescence) and adult services, without an intermediate “adolescence-to-adulthood transition” area that takes into account the clinical and developmental characteristics typical of young people (33–36). In addition, young people often hesitate to seek help for mental health problems due to stigma (social and self-stigmatization), shame, or fear of judgment (33–36). At the same time, services are often inadequate or not designed for “transition and flexibility” as a youth-centered model would require, resources are limited with difficulties in funding and maintaining dedicated units, and there is a lack of continuity between hospital settings and community services (33–36). Our protocol may help to fill this gap by proposing an integrated and systematic model that is not limited to the transmission of information but includes communication, social and problem-solving skills, which are particularly relevant in a vulnerable developmental phase such as adolescence. One of the main strengths of this study is the multimodal and transdiagnostic approach adopted. The use of thematic modules on emotions, anxiety, psychotic experiences, addictions, sleep and therapies allows us to intervene on clinical dimensions commonly manifested in youth emotional and affective disorders, supporting the growing trend towards a more dimensional approach towards youth psychopathology (37–40). Furthermore, the continuation of the intervention (in-person or via teleconference) even after discharge promotes continuity of care, a crucial element in preventing relapses and consolidating the therapeutic alliance. The study design, which includes a comparison with a control group receiving the usual treatment and a specific educational activity, will allow us to assess whether the experimental approach has added value compared to basic health information alone. This approach will not only verify the efficacy of the intervention but also identify which specific psychopathological dimensions are most influenced by psychoeducation.

This study has some potential limitations. First, it is a pilot trial with a relatively small sample recruited from a single centre, factors that could potentially limit the generalisability of the results. However, if the results confirm the expected efficacy, the protocol may serve as a model that can be replicated in other hospital and community settings, helping in increasing evidence at its support, with significant implications for the secondary and tertiary prevention of adolescent psychiatric disorders. At the same time, the diagnostic heterogeneity of participants could lead to an increased variability in outcomes and make it difficult to interpret results. However, this reflects the clinical reality of patients admitted to our ward in this age group, which cannot be excluded. Accordingly, the primary aims of this study are to evaluate feasibility and preliminary efficacy, rather than disorder-specific treatment effects. Furthermore, the target population, consisting of adolescents and young adults in the acute phase, may experience levels of emotional instability that could affect their consistent participation in sessions and completion of follow-up assessments. At the same time, systematic feedback from participants, collected through satisfaction questionnaires, will allow the programme to be further refined to better meet the needs of young users, improving the intervention and promoting patients engagement. A further limitation concerns the possible confounding effect of concomitant pharmacological and psychotherapeutic treatments, which are difficult to control in a real clinical setting. Although we recognize that in a natural clinical setting, complete control of concomitant treatments cannot be guaranteed, measures will be taken (detailed recording of treatment regimens, statistical control, and subgroup analysis) to minimize variability caused by treatment changes and to strengthen the reliability of causal inferences in this protocol.

However, such limitations are common in adolescent psychiatry research and do not preclude the usefulness of a pilot study for exploratory purposes. The early integration of psychoeducation, social skills and problem-solving strategies may help to modify the developmental trajectory of emotional disorders and has the potential to reduce recurrent hospitalisations, improving quality of life and promoting a greater sense of personal competence. Finally, this study aims to test an innovative and rigorously structured psychoeducational intervention, which could potentially represent a valuable complementary therapeutic option in acute psychiatric services for adolescents. The adoption of an integrated and participatory approach is a significant step towards the development of more effective, personalised treatment pathways aimed at preventing chronicity in the early stages of mental illness in young people.

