## Methods

2

A pilot single-centre randomized controlled intervention study was developed to be carried out at the Transition Psychiatry ward (specifically addressed to adolescents and young adults aged 15-24), Unit of Clinical Psychiatry, Department of Neurosciences/DIMSC, University Hospital of Marche Region within the Polytechnic University of Marche, Ancona, Italy. The randomization procedure will be performed using IBM Statistical Package for Social Sciences software, version 26 (SPSS, Chicago, Illinois, USA). For each participant, a random number will be generated using the RV.UNIFORM(0,1) function, which produces values distributed uniformly between 0 and 1. The cases will be then sorted according to the random number obtained and will be assigned to the two experimental groups in a 1:1 ratio. The allocation sequence will be generated by an independent researcher not involved in recruitment or intervention delivery, in order to ensure concealed allocation and minimize possible bias. The entire procedure will be documented to ensure replicability and methodological transparency.

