Patients referred to the inpatient Transition Psychiatry unit will be invited to participate in the study if they meet the following inclusion criteria: a) diagnosis of an emotional and/or affective Disorder (i.e., Major Depressive Disorder, Bipolar Disorder, Cyclothymia, Persistent Depressive Disorder, Seasonal Affective Disorder, Disruptive Mood Dysregulation Disorder, Other Specified Depressive Disorder, Unspecified Depressive Disorder, Other Specified Bipolar and Related Disorder, Unspecified Bipolar and Related Disorder, Unspecified Mood Disorder, Oppositional Defiant Disorder, Intermittent Explosive Disorder, Conduct Disorder, Other Specified Disruptive, Impulse-Control, and Conduct Disorder, Unspecified Disruptive, Impulse-Control, and Conduct Disorder) according to the Diagnostic and Statistical Manual of Mental Disorders, Fifth Edition text revised (DSM-5-TR) (15); b) aged 15–24 years old; c) admitted to the acute unit of Transition Psychiatry and expressed the willingness to participate to all the psychoeducational program also in the post-discharge sessions; d) agreement to the study participation during the 12-months follow-up period; e) ability to provide written informed consent (their parents in case they are less than 18 years old). This broad inclusion strategy was adopted to reflect the heterogeneous and often overlapping nature of early psychopathological manifestations during the transition age. In particular, the use of DSM-5-TR diagnoses should consider a dimensional and transdiagnostic framework, because symptom presentations in youths frequently evolve over time and may not yet conform to stable categorical boundaries. Anyways, if a patient is admitted to our department without a prior diagnosis, study inclusion is based on the preliminary diagnosis formulated at admission to our ward. Exclusion criteria will include: a) presence of an intellectual disability and/or mental retardation and/or difficulty in understanding Italian language and/or learning and/or moderate-to-severe cognitive deficits (absolute contraindication); b) patients with current uncontrollable psychomotor agitation and/or current drug and/or alcohol intoxication which may interfere with attention and/or concentration during the psychoeducational sessions (relative contraindication); c) the presence of an acute psychiatric symptomatology which may impact the level of consciousness and/or induce a temporary alteration of cognitive ability (relative contraindication). All included participants will continue to receive the treatments usually provided (e.g., regular psychiatric visits, pharmacological treatments, and psychotherapy). The study will be carried out in accordance with globally accepted standards of good practice and in agreement with the Declaration of Helsinki and with local regulations. An informed consent form will be signed by their parents after full description of study protocol. The study investigators will ensure that all mental health professionals involved in the study are qualified and informed about the protocol, interventions, and trial-related duties. An ethical approval request has been submitted (ID study: 4696) to our local Institutional Ethical Committee of Marche Region and will be obtained before starting with the recruitment.

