## Statistical analysis

5

Sample size has been calculated using the Statistical Software G*Power version 3.1. (Franz, Universitat Kiel, Germany). Based on the primary objective of the study, in order to detect any difference in the mean scores of the subscales of the DERS between the control and the experimental groups, by keeping a statistical power of 0.95 to identify an effect size of 0.8 (α=0.05, two-tailed) and taking into consideration all variables to be entered in the t-test. A total sample size of 84 was established to be reached for the present study (42 participants for each group). Considering the longitudinal follow-up and the clinical instability of the study population, attrition and missing data are expected. Analyses will be conducted on available data, with attrition rates systematically reported. Given the pilot nature of the trial, results will be interpreted with a focus on feasibility and preliminary efficacy. The IBM Statistical Package for Social Sciences software, version 26 (SPSS, Chicago, Illinois, USA), will be used for the data analysis. Descriptive analyses will be performed to describe the socio-demographic characteristics of the sample and to assess the normality of the data. Categorical variables will be summarized as frequency (n) and percentage (%), while continuous variables will be summarized as mean and standard deviation (SD). Categorical variables will also be compared using the χ^2^-test and *post-hoc* tests. To summarize the data and test the differences based on categorical analysis, parametric tests (t-test or ANOVA) or non-parametric tests (Kruskal-Wallis test or Mann-Whitney U test) will be used, depending on the normality of the data. To compare longitudinal data, the paired t-test or Wilcoxon test will be used, again based on normality. Finally, correlation and regression analyses (univariate/multivariate, linear/logistic) will be conducted, including socio-demographic and clinical variables and the total scores and subscales of the various scales, to explore any relationships between the different factors. The statistical significance cut-off will be set at p <0.05.

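### Diagnosis is named as a source of outcome variability, but the between-arm DERS comparison is unadjusted and the planned regression is not tied to it

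*Protocol article*

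**What the plan says.** - **Eligibility (Methods).** The listed diagnoses run from depressive and bipolar disorders to oppositional defiant, intermittent explosive and conduct disorders. The breadth is deliberate: "This broad inclusion strategy was adopted to reflect the heterogeneous and often overlapping nature of early psychopathological manifestations during the transition age". A patient without a prior diagnosis enters on the preliminary one made at admission.
- **Allocation (Methods).** Cases are "sorted according to the random number obtained and will be assigned to the two experimental groups in a 1:1 ratio". No stratification factor is named.
- **Sample size (Statistical analysis).** The calculation is for a t-test of DERS subscale means between the arms, with a two-sided α of 0.05, power 0.95 and a standardised effect of 0.8. The result is 84 patients, 42 per arm.
- **Group comparison (Statistical analysis).** Depending on normality, "parametric tests (t-test or ANOVA) or non-parametric tests (Kruskal-Wallis test or Mann-Whitney U test) will be used". No covariate is attached.
- **Regression (Statistical analysis).** Univariate and multivariate regressions with socio-demographic and clinical variables are planned, with the stated purpose of exploring relationships between factors.
- **Limitations (Discussion).** The protocol says that "the diagnostic heterogeneity of participants could lead to an increased variability in outcomes and make it difficult to interpret results". Its answer is that the mix reflects the ward's patients and that "the primary aims of this study are to evaluate feasibility and preliminary efficacy, rather than disorder-specific treatment effects". Statistical control and subgroup analysis are promised for concomitant treatments; diagnosis is not mentioned there.

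**The concern.** The sponsor identifies a baseline variable that it expects to affect the outcome, and it holds that variable for every patient before randomisation. The comparison that will carry the efficacy conclusion does not use it. Two things follow if the diagnostic classes differ in DERS level or recovery. The between-class variance stays in the error term and widens the confidence interval. Any chance difference between the arms in diagnostic mix also passes straight into the estimated effect.

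Limiting the aims to overall rather than disorder-specific effects does not deal with this. A diagnosis term in the model does not estimate disorder-specific effects; it sharpens the single overall contrast that the protocol keeps as an aim. The plan already contains a suitable tool, multivariate regression, but has not assigned it to the arm contrast.

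**Working it through.** **1. The plan's own figure.** Inputs from Statistical analysis: standardised effect d = 0.8, two-sided α = 0.05, power 0.95, t-test. For n per arm, power comes from the noncentral t distribution with 2n − 2 degrees of freedom and noncentrality d·√(n/2).
- n = 42: noncentrality 0.8 × √21 = 3.67, power 0.952.
- n = 41: power 0.947.

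So 42 per arm (84 in total) is the smallest size that reaches 0.95. The stated figure reproduces.

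**2. Assumptions.** The protocol gives neither the diagnostic mix nor the DERS gap between classes. I assume two classes (depressive/bipolar; disruptive/impulse-control/conduct), a share p of 30-40% in the second (25 or 34 of 84), and a gap δ of 0.5 to 0.8 within-class SD.

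**3. Chance imbalance with an unstratified 42/42 split** (exact hypergeometric):

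| Patients in second class | Arms differ by ≥10 points | ≥15 points |
|---|---|---|
| 25 of 84 | 34% of trials | 15% |
| 34 of 84 | 27% | 12% |

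The shift in the estimated effect is δ × imbalance. For 15 points it is 0.5 × 0.15 = 0.075 SD, or 0.8 × 0.15 = 0.12 SD. The standard error of the arm difference is √(2/42) = 0.218 SD, so the shift is about 0.34 or 0.55 of one standard error.

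**4. Validity of the unadjusted test.** In 20,000 simulated trials with no treatment effect (50% share, 0.8 SD gap), the t-test rejected in 4.8%, so the overall type I error is nominal. Among the 13% of trials with an imbalance of at least 19 points it rejected in about 9%.

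**5. Variance explained by diagnosis.** R² = p(1 − p)δ² / [1 + p(1 − p)δ²].
- p = 0.3, δ = 0.5: 0.0525 / 1.0525 = 0.050
- p = 0.4, δ = 0.5: 0.0600 / 1.0600 = 0.057
- p = 0.3, δ = 0.8: 0.1344 / 1.1344 = 0.118
- p = 0.4, δ = 0.8: 0.1536 / 1.1536 = 0.133

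**6. Power with 42 per arm.** Adjustment multiplies the residual SD by √(1 − R²), so d becomes d / √(1 − R²).

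| R² | Power at d = 0.8 | Power at d = 0.5 |
|---|---|---|
| 0 (unadjusted) | 0.952 | 0.620 |
| 0.050 | 0.961 | 0.642 |
| 0.057 | 0.962 | 0.645 |
| 0.118 | 0.971 | 0.674 |
| 0.133 | 0.973 | 0.682 |

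The degree of freedom spent on the extra term changes these values by no more than 0.0002. The d = 0.5 column shows what happens if the true effect is smaller than planned. These gains are for diagnosis alone. Once baseline DERS is also in the model, diagnosis adds less, by an amount that the protocol does not allow one to compute.

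**The case against.** The strongest reply is that nothing here is an error. The protocol discloses the heterogeneity, justifies broad inclusion and limits its aims to match. Unstratified randomisation followed by an unadjusted test is a valid design for a single-centre pilot. The shift from a plausible imbalance is a fraction of a standard error and small against 0.8 SD, and every input to that figure is assumed. Covariates are often left to an analysis plan, which is not shown here. Some diagnoses are preliminary, and the protocol itself says that presentations at this age may not fit stable categories, so a two-class factor is noisy.

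Most of this stands, and it rules out three stronger readings.
- A reader might infer that the plan cannot adjust for diagnosis. It can: multivariate regression with clinical variables is planned. It is simply not attached to the DERS arm comparison.
- A reader might infer that the trial falls short of 0.95 power. That requires d = 0.8 to be expressed in within-class SDs, which the protocol does not say. On the ordinary reading, power is 0.952.
- A reader might infer that unstratified allocation is a fault. It is acceptable here.

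The reply does not remove the narrower point. The article does more than stay silent about covariates: it names the family of tests for group comparisons and gives regression a different purpose. A noisy factor fixed at baseline still does no harm to the validity of the comparison.

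**Conclusion.** The point holds in a limited form. The named DERS comparison leaves out a baseline variable that the protocol itself links to outcome variability, and the regression that could use it is exploratory only. The cost is precision, plus exposure of the one realised trial to whatever imbalance occurs; it is not a loss of validity or a shortfall in sample size.

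Under the assumed shares (30-40%) and gaps (0.5-0.8 SD), adjusting for diagnosis alone gains about 1 to 2 percentage points of power at the design effect and about 2 to 6 points at an effect of 0.5. If the classes hardly differ on DERS, the gain is close to nil. The change is worth making because it is nearly free and also settles in advance how an imbalance in diagnosis will be handled.

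**What to change.** State in Statistical analysis that the main between-arm DERS comparison is a linear model of post-intervention DERS on arm, baseline DERS and a two-level admission-diagnosis group: depressive/bipolar versus disruptive/impulse-control/conduct. Assign every listed diagnosis to one of the two groups beforehand, and use the diagnosis recorded at entry even if it is later revised. The t-test or rank test can remain as a supporting analysis and the other regressions can stay exploratory.

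The cost is one degree of freedom for the diagnosis term and a coarse grouping of diagnoses that are sometimes preliminary. The sample size stays at 84. Methods says that ethics approval is to be obtained before recruitment starts, so the change can be made before any data exist.

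Stratifying the allocation by the same factor is optional. It would need blocks within strata, because the number of patients in each stratum is unknown in advance and a single random sort per stratum does not secure balance.

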Unusual experiences [figure not shown]	It provides information regarding the manifestation of different “unusual experiences” that patients may develop like dissociation, derealization, depersonalization or hallucinations.
Drugs and addictions [figure not shown]	It aims to raise awareness about substances and their associated risks, offering alternative coping strategies to substance use and addressing possible behavioral addictions, particularly digital ones.
Sleep and Biological Rhythms [figure not shown]	It provides information about sleep mechanisms, proper sleep hygiene, factors influencing sleep quality (both positively and negatively), and strategies to improve rest.
Medications [figure not shown]	Available pharmacological and non-pharmacological treatments for mental disorders, indications, side effects and strategies to cope with them, treatment duration, risk factors for relapse, and effects related to abrupt discontinuation of the therapy.

All images were generated using AI.

The sessions will take place each day for a total of 12 sessions for a period of around 2 weeks. Between sessions, participants will be invited to fill out dedicated practical exercises (“homeworks”). Each session will be organized into three phases: a) the first phase will be dedicated to clarifications and questions regarding the topics previously discussed; b) the second phase will focus on the main topics of the session; and, c) in the final phase, the key points addressed during the session, will be summarized with the assignment of target homeworks to all group members. A dedicated training material will be provided to all staff members in order to guarantee the fidelity of administration of all sessions of the experimental intervention, after providing a formal training by an experienced trained clinician (**Supplementary Material 1**). At the end of each session, all participants will complete a satisfaction questionnaire in order to improve and adapt the intervention based on participants’ feedback. **Supplementary Material 2** shows the satisfaction questionnaire that has been specifically developed. At the end of each session, participants will receive informative leaflets and cards summarizing the key-points addressed during the session (**Supplementary Material 3**).

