**Figure 1 f1:**
[figure not shown]
Timeline of the study.

At the baseline will be collected socio-demographic (e.g., sex, age, educational level, occupational and living condition) and clinical characteristics (e.g., age of onset, illness duration, number of affective and/or emotional episodes and previous hospitalizations, age at first hospitalization, comorbid physical and/or mental disorder, family psychiatry history, suicidality, drug and/or alcohol use current and/or previous, current and/or previous pharmacological and/or psychosocial and/or psychotherapy interventions) of all eligible participants through validated assessment tools. Researchers who administer assessment tools, will be blinded to patient allocation. All patients will be assessed at the following time points: a) at T0 (baseline), at least 1 day before the start of the intervention; b) at T1 (post-intervention); c) at T2 (follow-up at 1 months after completion of intervention); d) at T3 (follow-up at 3 months after completion of intervention); and, e) at T4 (follow-up at 6 months after completion of intervention); f) at T5 (follow-up at 12 months after completion of intervention). During the assessment, whereas the participant feels distressed or exhausted, the assessment will be postponed in another moment in a range of 2–3 days.

At baseline, participants will be administered the following assessment tools: Difficulties in Emotion Regulation Scale (DERS) (18), Brief Psychiatric Rating Scale (BPRS) (19), Clinical Global Impression Scale - Severity (CGI-S) (20), Coping Orientation to Problems Experienced-New Italian Version (COPE-NVI) (21), Global Assessment of Functioning (GAF) (22), Internalized Stigma of Mental Illness Inventory (ISMI) (23), Mental Health Knowledge Schedule (MAKS) (24) and the Montreal Cognitive Assessment (MoCA) (25) (**Tables 2**, **3**).

**Table 2 T2:** Timeline of the assessment administration.

Assessment	T0	T1	T2	T3	T4	T5
DERS	X	X	X	X	X	X
BPRS	X	X	X	X	X	X
CGI-S	X	X	X	X	X	X
CGI-I		X	X	X	X	X
COPE-NVI	X	X	X	X	X	X
GAF	X	X	X	X	X	X
ISMI	X	X	X	X	X	X
MASK	X	X	X	X	X	X
MOCA	X					

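### Controlling for or subgrouping on concomitant treatment changes can bias the resulting estimates and does not strengthen causal inference; both should be limited to treatment recorded at baseline

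*Protocol article*

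**What the plan says.** Section 6 (Discussion) of the protocol article names as a limitation the "possible confounding effect of concomitant pharmacological and psychotherapeutic treatments, which are difficult to control in a real clinical setting". It then says that measures will be taken. After the recording of regimens these are "statistical control, and subgroup analysis) to minimize variability caused by treatment changes and to strengthen the reliability of causal inferences". It does not say when the treatment variable is measured or which analysis it enters.

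Other parts of the article bear on this:

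- **Section 2 (Methods):** allocation is 1:1 at random, and "All included participants will continue to receive the treatments usually provided".
- **Section 3.2:** assessments run from T0 to T5, 12 months after the intervention ends. The baseline record includes "current and/or previous pharmacological and/or psychosocial and/or psychotherapy interventions".
- **Table 1:** the experimental Medications module covers, among other things, "treatment duration, risk factors for relapse, and effects related to abrupt discontinuation of the therapy".
- **Section 6, opening paragraph:** structured interventions of this kind "may offer substantial advantages in terms of treatment adherence, illness awareness, mental health literacy", and the tools psychoeducation offers are called "essential for promoting awareness, empowerment, and greater adherence to treatment".
- **Table 4:** the control arm also has a medication module, and it too stresses adherence.
- **Section 5:** the trial is sized on a two-group t-test. Regression is there to explore relationships, using socio-demographic and clinical variables. No concomitant-treatment covariate or subgroup is named.

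**The concern.** Treatment in place before allocation is balanced between the arms in expectation, so it does not confound the randomised comparison. A change in drugs or psychotherapy after allocation is something else: an intercurrent event, and a possible mediator if the intervention influences it. The article itself supplies a plausible route, since the experimental arm is taught about medication and is expected to adhere better.

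Adjusting for such a change, or splitting patients by it, can do two things. It can remove the part of the effect that runs through treatment. It also compares patients who are no longer alike, because unmeasured severity may drive both the treatment change and the outcome. The resulting estimates would then be presented as causally stronger than the plain randomised comparison, when they are weaker.

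**Working it through.** **The plan's own figure.** Section 5 states effect size 0.8, two-sided α = 0.05, power 0.95, and 42 per group. The noncentral-t calculation gives 41.59, rounded up to 42 per arm or 84 in total, with power 0.952. The figure reproduces and is not in dispute. It also shows that the planned comparison is a two-group test without covariates.

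**Model for conditioning on treatment change.** Let T be the randomised arm, U unmeasured severity, M the treatment change after randomisation, and Y the outcome in SD units, with a positive arm effect counted as benefit:

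- M = aT + gU + error, with variance 1 within arm
- Y = dT + bM + qU + error

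The steps are:

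1. The total effect of allocation is d + ab. The unadjusted randomised difference estimates this.
2. Given T and M, the expected value of U is g(M − aT). Substituting, the coefficient of T adjusted for M is d − agq.
3. The bias against the total effect is (d − agq) − (d + ab) = −a(b + gq).

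**Inputs.** The documents give no value for a, b, g or q, so every value below is an assumption. Simulated values come from 1,000,000 records.

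| a | b | g, q | Total effect | Bias −a(b + gq) | Adjusted effect | Simulated: unadjusted / adjusted |
|---|---|---|---|---|---|---|
| 0 | 0.3 | 0.5, 0.5 | 0.80 | 0 | 0.80 | 0.807 / 0.807 |
| 0.5 | 0.3 | 0, 0 | 0.80 | −0.5 × 0.30 = −0.150 | 0.650 | 0.799 / 0.648 |
| 0.5 | 0.3 | 0.5, 0.5 | 0.80 | −0.5 × 0.55 = −0.275 | 0.525 | 0.802 / 0.526 |
| 0.5 | 0 | 0.5, 0.5 | 0.80 | −0.5 × 0.25 = −0.125 | 0.675 | 0.801 / 0.675 |
| −0.5 | 0 | 0.5, 0.5 | 0.80 | +0.5 × 0.25 = +0.125 | 0.925 | 0.803 / 0.926 |
| 0.5 | 0 | 0.5, 0.5 | 0 | −0.5 × 0.25 = −0.125 | −0.125 | 0.003 / −0.122 |

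The unadjusted difference recovers the total effect in every row, up to simulation error.

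**Signs.** Direction depends on signs that nobody knows in advance. If severity prompts more treatment and worsens the outcome, gq is negative. With a = 0.5, b = 0 and gq = −0.25, the bias is −0.5 × (−0.25) = +0.125 and the adjusted effect 0.925. With b = 0.3 it is −0.5 × 0.05 = −0.025, giving 0.775.

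**Subgroups.** Splitting on M at zero in the third row gives arm differences of 0.642 and 0.616 against a true 0.80. Subgrouping therefore carries the same problem as adjustment.

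**The case against.** The case on the other side has four parts.

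- **Timing is inferred.** Section 6 names the source of variability, not the covariate. Control and subgroups based on T0 treatment would fit its words and would be valid. This stands as a caution. But the stated target is change, in a trial where usual care continues, and nothing in the article limits the analysis to baseline.
- **The arms may not differ.** Table 4 shows that the control arm is also taught about medication and adherence. This stands. If a = 0 there is no bias in this model, and the size and sign of a are unknown.
- **Adherence is not regimen change.** The expected benefit concerns adherence, no adherence scale appears in Table 2, and nothing says adherence will be adjusted for. This stands in part. The route from allocation to treatment change is plausible but indirect.
- **The sentence sits in a limitations paragraph of a pilot.** Section 5 keeps regression exploratory. This also stands, and it sets the limit of the point.

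A reader might go further and infer that the trial's main effect estimate is biased, or that power collapses. For instance, if half of 0.8 ran through treatment change, a t-test at 0.4 would have power of about 0.44. The documents do not support either inference. Section 5 describes a between-group test with no treatment covariate. The one-half share is invented, and that power figure is for an unadjusted test, not for a covariate-adjusted model.

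**Conclusion.** The point holds in a conditional form. On its natural reading, Section 6 commits to conditioning on treatment changes after randomisation and gives causal inference as the reason. That rationale is unsound, because such conditioning can bias the adjusted or subgroup estimate in either direction.

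The bias could be nil. Over the tabulated inputs a true 0.80 becomes about 0.53 to 0.93, and a true zero can become about −0.13. These figures rest on a linear model and on path values that the documents do not supply. They show that the bias can matter and do not predict its size in this trial. The conclusion covers the adjusted and subgroup analyses announced in Section 6; the Section 5 comparison is not shown to be affected.

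**What to change.** Amend Sections 5 and 6 along these lines:

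> Statistical control and subgroup analyses for concomitant treatment will use only treatment recorded at T0. The effect estimate is the comparison by randomised arm, unadjusted or adjusted for baseline variables. Changes in drug treatment or psychotherapy after randomisation will be described by arm, and any analysis conditioning on them will be labelled exploratory.

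The phrase about strengthening causal inference should then be attached only to the baseline-adjusted analysis, or dropped.

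The cost is about a sentence in each section. No new data are needed: T0 treatment is already collected under Section 3.2, and Section 6 already promises to record regimens. What is given up is the removal of outcome variability due to later treatment changes from the effect estimate. That variability belongs to the effect of allocation under continuing usual care.
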